# Analgesic effect of auricular point acupressure for acute pain in patients with dementia: study protocol for a randomized controlled trial

**DOI:** 10.1186/s13063-022-06326-5

**Published:** 2022-05-14

**Keywords:** Acute pain, Analgesic, Auricular point acupressure, Dementia

## Abstract

**Background:**

Common and frequent as acute pain is, it is often underestimated and undertreated in older people with dementia in nursing homes and inadequate pain management remains an issue.

**Methods:**

The study is designed to be a randomized, sham-controlled trial and is underway in nursing homes located in China. A total of 206 dementia patients are being recruited from nursing homes in Yinchuan, China. They are randomly allocated to an intervention or a controlled group in a 1:1 ratio. The intervention group will be treated with true APP therapy, while the other group will receive APP at sham point stimulation therapy. The patients will be assessed at baseline (T0), at 5 min during performing the intervention (T1), and at 5 min after completion of the intervention (T2). The primary outcome is the level of pain relief at T1 and T2. Physiological parameters, side effects and additional use of analgesics during the procedure, satisfaction from caregivers, and acceptance of patients are evaluated as secondary outcomes.

**Discussion:**

The results of this study are expected to verify the analgesic effect of APP for acute pain in patients with mild dementia in nursing homes. It has the potential to prompt APP therapy to be implemented widely in dementia patients with acute pain in nursing homes.

**Trial registration:**

Chinese Clinical Trial Registry ChiCTR2100047932. Registered on 27 June 2021. Currently, patient recruitment is ongoing. Recruitment is expected to take place from December 2020 to December 2021.

## Introduction

For residents in the nursing home, dementia and pain have aroused great public concern and a lot of discussions in the global medical policy, research and education fields for many years [1]. Pain is a common experience for many older adults with dementia in nursing homes. It is estimated that the prevalence of pain in dementia patients residing in the nursing home is 19–83%, and the pain they are suffering is difficult to assess and inadequately treated [2–4]. There is also a guideline that indicates that the incidence of acute pain is as high as 75% in elderly care facilities, but even higher for chronic pain [5]. Furthermore, uncontrolled pain causes many detrimental consequences for patients with dementia in nursing homes, such as distressing psychological, social isolation, daily activity and function limitation, sleep disturbances, hospital stays prolonging, and medical expenses increasing [6–8]. In particular, acute pain in elderly patients can have a serious impact on psychology and even lead to an attempt to suicide [8].

Acute pain is common and frequent, but it is often underestimated and undertreated in elderly people with dementia in nursing homes. Therefore, poor pain management in this population remains a problem [4]. Complications of acute pain have been well documented. However, few clear guidelines are currently available on the optimal therapies to measure and treat acute pain in patients with dementia in nursing homes [6]. Pharmacological and non-pharmacological modalities have been practiced to manage acute pain and its associated complications in older adults with dementia over the past decade. It is advised that pharmacological treatment to control acute pain in the elderly should generally follow a three-step scheme: paracetamol, non-steroidal anti-inflammatory drugs (NSAIDs), opioids, and the other adjuvant drugs. Although paracetamol is recommended worldwide as a first-line pain reliever for patients with dementia in nursing homes, there are limited reports on its analgesic effects [9]. Several studies have also evidenced that elderly persons with dementia are prescribed fewer NSAIDs and other analgesics than those without dementia in nursing homes, and there are not many opportunities to consider the use of strong analgesics [9, 10]. Patients with dementia are prescribed opioid analgesics, even though the doses they were allowed to take are one-third of those who are cognitively intact elder adults, especially in the nursing home residents with dementia [11, 12]. There is little evidence of the effectiveness of adjuvant drugs, such as anti-inflammatory drugs, anticonvulsants, and antidepressants, for relieving acute pain in older adults with dementia in nursing homes [11]. Furthermore, they are more prone to have drug-related side effects [7]. These factors also contribute to poor acute pain control in patients with dementia in the nursing home.

Therefore, it is important to seek non-drug therapies for controlling dementia patients with acute pain. Traditional Chinese medicine (TCM) theory holds that non-pharmacological methods, such as acupoint acupressure, acupuncture, massage, psychotherapy, and electroshock therapy, play a positive and important role in the treatment of acute pain. Non-pharmacological interventions have become the priority for patients with acute pain due to fewer side effects, non-invasive, and better safety [13]. According to TCM theory, the ear is where the body’s meridians (the main twelve meridians: six of which are yin meridians and six yang meridians) connect and where the essential Qi converges. So, stimulating auricular points can activate Qi and blood circulation, dredge the meridians, and then achieve the purpose of analgesia [14]. Stimulating auricular acupoints can regulate the secretion of central neurotransmitters, thereby activating the analgesic system in vivo. In other words, it exerts a pain-relieving effect by activating the downward pain inhibitory pathway and thus inhibiting the upward pain pathway in the brainstem [14]. Systematic review and meta-analysis also reported that APP showed promising results in pain relief in the experimental group compared with the control group [15, 16]. APP therapy has been widely applied in various types of pain, such as acute postoperative pain, pain related to dental, and musculoskeletal pain in older adults, and as an adjunct analgesic among cancer patients [15–17]. A dearth of the study explored that APP therapy is applied to control acute pain in nursing home residents with dementia. Therefore, a randomized, sham-controlled trial was designed to evaluate the analgesic effect of APP for senile dementia patients with acute pain in nursing homes.

## Methods

### Study design

This study is a multi-center and single-blind, randomized, sham-controlled clinical trial. It aims to compare and analyze the one-time analgesic effect between the intervention group and the sham-controlled group (Fig. 1, Table 1) for acute pain in patients with dementia. This trial, superiority framework, was designed on the basis of SPIRIT guidelines and the Consolidated Standards of Reporting Trials (CONSORT) statement [18, 19]. The Ningxia Medical University Ethics Committee has given its official approval for the study protocol, which has been registered at the Chinese Clinical Trial Registry (No.: ChiCTR2100047932). Each patient will be given a detailed explanation by the researcher including the purpose, benefits, and potential risks of the study. Moreover, they can withdraw from the study at any time, and this will not affect medical services other than the research. Subsequently, the qualified recruits who signed informed consent entering the study will receive APP or shamed APP treatment by an investigator, a master candidate in nursing science with APP professional training. It is needed to make important protocol modifications to reduce underpower of the study protocol and increase patient safety. We will communicate with the Data Management and Safety Monitoring Committee (DMSMC), all participants, and the Ethics Committee.

**Fig. 1 Fig1:**
[figure not shown]
Study design framework. BP, blood pressure; HR, heart rate; SpO_2_, oxygen saturation; APP, auricular point acupressure; Score of pain, the Face Pain Scale Revised

**Table 1 Tab1:** Schedule of enrollment, interventions, and assessments

Procedure	Study period			
	Enrolment	Post-allocation		
	Dementia patients with acute pain	T0	T1	T2
Enrolment				
Eligibility screen	×			
Informed consent	×			
Allocation	×			
Interventions				
Control group			×	×
Treatment group			×	×
Assessments				
Face pain scale revised	×	×	×	×
Blood pressure		×	×	×
Oxygen saturation		×	×	×
Heart rate		×	×	×
Satisfaction				×
Acceptance				×
Side effect			×	×
Additional use of analgesics during the intervention				×

### Study setting

This randomized controlled trial is being conducted at three nursing homes in Yinchuan, China. These institutions are urban and public in the region, with approximately 2000 permanent residents.

### Patients

All 206 patients who met the inclusion and exclusion criteria are being recruited from the three nursing homes. Recruitment is expected to take place from December 2020 to December 2021. The recruits with informed consent before entering research will be randomly allocated to an intervention or a sham-controlled group in a 1:1 ratio. Furthermore, it is feasible to have enough patients to meet the target sample size in three nursing homes. The inclusion criteria include the following: (1) aged 60 or above with speaking Chinese, (2) dementia was diagnosed by the Diagnostic and Statistical Manual of Mental Disorders (DMS-V) criteria [20], (3) diagnosis of mild dementia based on the Montreal Cognitive Assessment (MoCA) [21], (4) acute pain and a score of pain ≥ 4 based on the Face Pain Scale Revised (FPS-R), (5) able to be monitored by pulse oximetry, (6) understanding the meaning of the FPS-R, and (7) volunteering to participate in the study and signing the informed consent (caregivers, patients, and/or family members). The exclusion criteria are as follows: (1) moderate or severe dementia, (2) medical contraindication for ear acupressure (inflammation, ulcers, frostbite in the ear), (3) history of allergy to adhesive tape and alcohol, (4) critically ill patients who have no response to the effectiveness and safety of new treatments (serious heart, brain, liver, kidney, or hematopoietic system diseases), and (5) patients who received drugs for pain management and other interventions. Once the subjects were enrolled, written informed consent from all patients and their caregivers was obtained by the researchers.

### Interventions

The intervention group will be planned to receive auricular-plaster therapy, with one piece of Semen Vaccariae® (about 2 mm in diameter, Taicheng Technology and Development Co., Ltd., Shanghai, China) attaching to the center of a piece of medical adhesive tape (6 mm × 6 mm). This study initially selected four active acupoints including shenmen (TF4), subcortex (AT4), adrenal (TG2P), and two auricular points corresponding to pain sites based on the Nogier auricular point diagram for managing pain [22]. A researcher will bring the required items to the participants’ bedside and assist them in taking the position that is easy to operate. Subsequently, the researcher holds the helix with the left hand and identifies sensitive points by virtue of an ear probe with the right. The medical adhesive tapes with Semen Vaccariae® will be pasted on the selected auricular points with forceps by the researcher after checking and sterilizing the skin of the patients’ ears using 75% alcohol. Then, each auricular point will be pressed gently 2 times lasting 1 min each time. There is no time interval during the operation unless adverse reactions occur or until finishing the procedure. The pressure should be moderate and enough within individual’s endurance (the subject feels swelling pain, numb, and warm sensation). After the whole intervention, these tapes will be removed. However, these five points (kidney, CO10; ocuiput, AT3; internal ear, L06; external ear, TG1u; adrenal gland, TG2P) were selected in the control group. The main effect of these five points was to delay hearing loss; its procedures are described in the intervention group. However, the subject simply experiences the warm sensation in their ears. Relevant concomitant care is permitted during the trial. Although adverse reactions associated with auricular acupressure are rare, in this study, if they occurred (side effects occur during the implementation, they are short-lived and mild [15, 16]) or the participant’s requirements that the intervention they receive be discontinued, researchers can determine whether the trial will continue. Furthermore, the reasons for the withdrawal will be logged. Strategies to improve adherence to intervention protocols will be applied in *Trials*. Prior to the protocol, researchers will describe the method and duration of the intervention and the potential risk involved to the participants in detail [23]. In the intervention, there are many patients’ physiological parameters monitored by the data collector. A supervised compliance form (SAF) for this study protocol is necessary to collate patient compliance [23].

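### Adrenal point TG2P is listed both as an active analgesic point and as a sham point, so the control arm may receive part of the treatment

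*Protocol article*

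**What the plan says.** The abstract describes a true-versus-sham comparison: one arm has true APP and "the other group will receive APP at sham point stimulation therapy". The Study design section places this in a superiority framework.

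The Interventions section defines both point sets. For the active arm: "This study initially selected four active acupoints including shenmen (TF4), subcortex (AT4), adrenal (TG2P), and two auricular points corresponding to pain sites", chosen "based on the Nogier auricular point diagram for managing pain". For the comparator: "these five points (kidney, CO10; ocuiput, AT3; internal ear, L06; external ear, TG1u; adrenal gland, TG2P) were selected in the control group". It then adds: "The main effect of these five points was to delay hearing loss; its procedures are described in the intervention group". On sensation, pressure in the active arm is to produce swelling-type pain, numbness and warmth within the patient's tolerance, whereas in the control arm "the subject simply experiences the warm sensation in their ears".

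Nothing in the article mentions that one point is in both lists.

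**The concern.** The same anatomical name and the same code carry two incompatible roles. In one list TG2P is active for pain. In the other it belongs to a set presented as sham, whose stated purpose has nothing to do with pain. A sham control is meant to reproduce the ritual and attention of treatment without the component under test. If it includes a point that the protocol itself classes as active, the trial no longer compares APP with a sham free of that component.

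What is at stake is mainly interpretation. The trial sets out to verify an analgesic effect and hopes to inform guidance. A positive result would not be undermined by this overlap. A null result would be ambiguous: it could mean that APP does not relieve pain, or that both arms received some of the same relief. Analysis cannot remove the ambiguity, because every control patient treated as written has TG2P pressed.

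**Working it through.** **Step 1: compare the lists (Interventions section).**

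| | Active arm | Control arm |
|---|---|---|
| Named points | TF4, AT4, TG2P | CO10, AT3, L06, TG1u, TG2P |
| Further points | two matched to pain sites | none |
| Number listed | 3 + 2 = 5 (text says four) | 5 |
| Stated purpose | managing pain | hearing |
| Procedure | two presses of 1 min per point | by reference to the active arm |
| Stated sensation | swelling-type pain, numbness, warmth | warmth only |

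TG2P is the only code in both lists. It is 1 of the 5 control points and 1 of the 5 listed active points.

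**Step 2: what the overlap does to the contrast.** Assume for illustration that point effects add. Let *t* be the relief from TG2P at the active stimulus, *w* (0 to 1) the share of that relief produced by the control stimulus, *g* the relief from the other active points, and *s* the relief from the other control points. Non-specific effects are taken as equal in both arms.

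- Difference against a sham without TG2P: (*g* + *t*) − *s*.
- Difference against the control as written: (*g* + *t*) − (*s* + *w t*).
- Attenuation: *w t*.

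The attenuation is zero if TG2P has no effect (*t* = 0) or if the control stimulus is too weak to matter (*w* = 0). It equals *t* if the stimulus is the same in both arms (*w* = 1). The documents give neither *t* nor *w*, so the range is 0 to *t*, with *t* unknown.

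**Step 3: does the sample size suffer?** The Sample size estimation section gives pilot FPS-R means of 5.97 (control) and 4.79 (intervention), a difference of 5.97 − 4.79 = 1.18. It does not say which points the pilot control received.

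- If the pilot used the same control, 1.18 already equals the difference with *w t* removed. The main trial targets that same quantity, and the overlap costs no power.
- If the pilot used a control without TG2P, the main trial would target 1.18 − *w t*.

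The documents do not say which case applies.

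**The case against.** The strongest reply is that the overlap is one point, possibly a misprint in one list, and that nothing shows it matters. No per-point effect is documented. The warmth-only sentence suggests a lighter stimulus in the control arm, so the shared relief may be partial or nil. The differing sensations could also reveal allocation to patients, which might push a self-reported pain score in the opposite direction. All of this stands, and it limits what can be said about size and net direction. It does not remove the contradiction. A misprint would still need correcting, because a reader cannot tell which list is right. The warmth-only sentence is itself hard to square with a procedure said to be the active arm's.

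Four stronger readings are tempting, and the documents do not support them:

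- *That any TG2P effect cancels out completely.* This needs an equal stimulus in both arms, which the sensation sentence puts in doubt.
- *That the trial loses power.* Shrinking 1.18 by an assumed share presumes that the pilot control did not contain TG2P, which is not stated.
- *That other control points (kidney, occiput, ear) may double as pain-site points.* This depends on the cited auricular diagram, which is not reproduced.
- *That pressing lasts 8 minutes in one arm (4 × 2 × 1) and 10 in the other (5 × 2 × 1).* The word four may count types of point, with two points of the pain-site type. That gives five points and 10 minutes in both arms.

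**Conclusion.** The point holds as a contradiction in the definition of the comparator: TG2P is both active and sham, without acknowledgement or justification. The consequence is conditional. On the protocol's own premise that TG2P is analgesic, and provided that the control stimulus delivers some of that effect, the contrast may be attenuated relative to a sham without TG2P. A null result would then not show that APP lacks an analgesic effect. The size is unknown, no loss of power is demonstrated, and the net direction of all influences on the comparison is not established. The point still matters because it concerns what the trial compares, and it is cheap to correct.

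**What to change.** Amend the Interventions section so that no point is labelled both active and sham, or, if TG2P stays in both lists, say so and justify it. Which points to use is for the clinical team.

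In the same edit, reconcile two neighbouring statements:

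- the announced four active points with the five listed;
- the statement that the control procedure is the active arm's with the different sensation stated for control.

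For patients treated under the current lists, describe the contrast in reports as APP against a control that includes TG2P, with possible attenuation towards the null, and do not read a null result as evidence of no analgesic effect. If a list changes while the trial is running, record whether each patient was treated before or after the change and account for this in the analysis.

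The cost is one text amendment and a sentence on interpretation. If the list changes mid-trial, it also needs one recorded indicator per patient. No further outcome data are needed.

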
### Randomization and blinding

Sequence numbers of the patients with dementia will be generated by a computer-produced random list, which is performed by a statistical expert from Ningxia Medical University. But she is independent of the trial. The randomization schedule in a sealed envelope will be kept in a dedicated research office. There are many strategies to ensure the concealment of data distribution and minimize selection bias as well as create a double-blind environment. It will be blind to the randomized lists for participants (e.g., other researchers, patients, and caregivers) except the investigator responsible for conducting the intervention [24]. The project manager can suspend blinding until all the trials have been carried out according to the rules. The research team is responsible for reducing the rate of loss of intervention. Prior to the trial, the researcher went into the nursing home and lived and worked with the caregivers of the elderly to learn about the patient’s lifestyle. Meanwhile, they obtained their and their caregivers’ support and cooperation. Patients and their caregivers will be presented face to face with detailed information, which includes intervention process, collection and use of data and biological specimens, benefits, and potential adverse reactions from the trial [23]. But patients also have the right to withdraw from the study at any time without affecting subsequent care. In case patients and (or) their caregivers decide to quit the trials, data and biological specimens will be destroyed. It has been also documented in the informed consent form.

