### Measurement

Each patient’s demographic data (age, sex, nationality, educational background, marital status, occupation before retirement, personal income per month, history of taking medicine, chronic case history) will be recorded by a self-designed questionnaire. Other information including physiological parameters (heart rate, blood pressure, and oxygen saturation), sore spot, pain score, adverse effects, the use of analgesics in the intervention, satisfaction of caregivers, and acceptance of patients, will be more rigorously documented. The MoCA is made to identify the severity of dementia among the patient. And locality of the pain will be shown clearly according to the Brief Pain Inventory Chinese version (BPI-C) [25]. The FPS-R with great reliability and validity will be elected to assess pain intensity, and three physiological parameters are monitored with electronic sphygmomanometer (OMRON, HEM-7120) and Fingertip Oximeter (PC-60B). The data required for the study include pain score, noninvasive monitoring of blood pressure, heart rate collected at baseline (before performing the intervention, T0), at 5 min during performing the intervention (T1), and at 5 min after the intervention finished (T2) as well as digital monitoring of oxygen saturation. The intervention process of APP should be closely monitored, even if there are no reports of its side effects. And it will be recorded in detail and properly handled for any adverse reactions observed. The use of analgesics in the intervention also will be carefully recorded to enhance analysis of the safety and analgesic effect of APP. Satisfaction from caregivers will be surveyed via a 5-point satisfaction scale (5, very satisfied; 4, satisfied; 3, uncertain; 2, dissatisfied; 1, very dissatisfied) at T2 [26]. However, acceptance of patients will be measured by just asking them if they would like to accept the APP treatment once again.

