### Management and safety monitoring

Prior to the study, research team members will receive a training program, which will cover the research design, procedure, evaluation of outcome measures, randomization, data collection, and data monitoring. For example, data recorders will be trained on how to collect and manage data to ensure the objectivity, quality, and safety of data as far as possible. Patients were anonymous throughout the trial. All subject’s personal information will also be stored in a separate envelope. It will then be saved in a Microsoft Access (Microsoft Office 2010, Redmond, WA, USA) database, which is password protected [23]. A separate code was generated by pre-randomization and kept by the project manager. It is a unique identifier that identifies anonymized data. With the consent of the project leader, only members of the research team have access to the collected information for a reasonable reason [24]. Another Microsoft Access database will be used to store all trial data. It can only be got by the data collectors, the investigator, and the DMSMC. It is necessary although the APP treatment was the least risky. It consisted of the project manager, principal researcher and physician of each sub-center, and experts from the Ethics Committee of Ningxia Medical University. They are primarily responsible for the quality control of clinical trials, including but not limited to the data collection and management and uniform training for investigators. Regular monitoring and auditing data will be also required. It should be also noted that the trained data collectors and investigators are fixed and that data quality control is carried out through double-entry bookkeeping by them [23, 24]. In addition, information on patients with withdrawal will not be included in the final analysis, and other researchers will investigate what led them to withdraw from the trial. According to previous studies, the side effects of this intervention have been reported rarely. Conducting an interim analysis or stopping rules will not be applied to the current study. All of the study subjects were elderly patients, so they will be closely monitored as part of the standard of care before, during, and after study participation.

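### The plan as described does not secure the blinding of the FPS-R recorder: the T1 score is taken while arm-specific tapes are on the ear

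*Protocol article*

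**What the plan says.** All references are to the protocol article.

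- **Blinding claim.** Randomization and blinding sets out to create a double-blind setting and states: "It will be blind to the randomized lists for participants (e.g., other researchers, patients, and caregivers) except the investigator responsible for conducting the intervention". The person recording outcomes falls among the other researchers and is thus presented as blind. Study design calls the same trial single-blind.
- **Who is present.** Interventions says that, while the treatment is being given, there are "physiological parameters monitored by the data collector". Primary outcome measure says that a researcher in charge of recording takes the pain score on the FPS-R.
- **When.** Measurement places T1 five minutes into the intervention and T2 five minutes after it ends. Pain score, blood pressure and heart rate are collected at both.
- **What is on the ear.** Tapes of 6 mm × 6 mm, each holding a seed, are fixed to the selected points, and "each auricular point will be pressed gently 2 times lasting 1 min each time", with no pause. "After the whole intervention, these tapes will be removed".
- **Which points.** The active arm uses "shenmen (TF4), subcortex (AT4), adrenal (TG2P), and two auricular points corresponding to pain sites". The control arm uses CO10, AT3, L06, TG1u and TG2P.
- **Staff.** Management and safety monitoring says that "research team members will receive a training program, which will cover the research design, procedure, evaluation of outcome measures, randomization, data collection, and data monitoring", and that data collectors and investigators do not change during the trial.

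**The concern.** Withholding a list blinds someone only if the list is the sole way to learn the arm. Here the primary outcome is scored partway through a bedside procedure, while the treatment is physically marked on the ear at sites that depend on the arm. A fixed recorder would meet the control pattern again and again. A recorder who works out the arm at T1 does not forget it by T2, so both primary time points are exposed.

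Someone must present the FPS-R to residents with dementia and write down the answer. Knowledge of the arm could colour how that is done, most plausibly in favour of true acupressure. This route is separate from the treating investigator's knowledge of the list. It is also separate from the different sensations expected in the two arms, which bear on the patient's blind.

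**Working it through.** The plan states no figure on this point, so there is none to reproduce. Three checks follow.

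**1. Is T1 before the tapes come off?** Inputs from Interventions: 2 presses per point, 1 minute each, no interval. The text announces four active points but lists three named points plus two pain-site points, so both counts are tried.

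- Pressing time = points × 2 × 1 min.
- Five points: 5 × 2 × 1 = 10 min.
- Four points: 4 × 2 × 1 = 8 min.

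T1 at 5 min falls mid-procedure either way. If the clock starts earlier, at positioning or taping, T1 comes earlier still and remains before tape removal.

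**2. Do the tape positions differ by arm?** Comparing the named points:

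| | Points |
|---|---|
| Both arms | TG2P |
| Active only | TF4, AT4 |
| Control only | CO10, AT3, L06, TG1u |
| Active, varying by patient | two pain-site points (not named) |

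The control pattern is the same in every control patient. The active pattern varies, but always includes TF4 and AT4.

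**3. What could a shift in the recorded score do?** This is an illustration. The documents give no size for such a shift, so 0.25 to 0.5 FPS-R points is assumed. Inputs from Sample size estimation: pilot means 5.97 and 4.79, SDs 1.81 and 1.96, 86 per group before and 103 per group after the drop-out allowance.

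- Pilot difference: 5.97 − 4.79 = 1.18. The assumed shift is 0.25/1.18 = 21% to 0.5/1.18 = 42% of it.
- Pooled SD: √((1.81² + 1.96²)/2) = 1.886.
- SE of the difference = 1.886 × √(2/n). For n = 86 it is 0.288; for n = 103 it is 0.263.
- With no true effect and a pure shift b, the two-sided rejection probability is Φ(b/SE − 1.96) + Φ(−b/SE − 1.96).

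| Per group | b = 0.25 | b = 0.5 |
|---|---|---|
| 86 | 14% | 41% |
| 103 | 16% | 48% |

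The nominal value is 5%.

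**The case against.** The strongest reply is that several links are inferred.

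- **Identity and view.** The article does not say that the data collector and the FPS-R recorder are one person, or where either stands. A cuff and a fingertip oximeter can be read without looking at the ear. This stands. But whoever takes the T1 pain score must be with the patient before the tapes come off.
- **Training.** The statement specific to data recorders concerns collecting and managing data. Nothing says they learn point locations. This stands too. The team-wide list does include procedure and randomisation, and does not exempt recorders.
- **Similarity of the arms.** Seed, tape and pressing routine are the same, TG2P is common to both, and there is no single active pattern. Decoding is therefore possible, not certain.
- **Self-report.** Patients must have mild dementia and must understand the FPS-R (Patients, inclusion criteria). That limits the recorder's influence without removing it.
- **Condensed article.** Screens and seating are details that a full protocol may hold, and the blinding section mentions many strategies. Silence about a screen alone would be no finding. The point rests on what is stated: a blinding mechanism that covers only the list, a measurement schedule that bypasses it, and two blinding labels that disagree.

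A reader might infer that the recorder is certainly unblinded, or that the blind cannot hold at all. The documents do not support that, because sight of the ear and knowledge of the points are not stated. A reader might also infer that caregiver satisfaction is biased by the same route. That is the caregiver's own 5-point rating, and no path from the recorder to it is shown.

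**Conclusion.** The point holds in limited form. As described, the blinding of the FPS-R recorder is not secured, and there is a credible route to unblinding at T1 that carries over to T2, so both primary time points are affected. The conclusion assumes that the ear can be seen at T1 and that the recorder can tell the patterns apart, through training or repeated exposure. Carry-over to T2 also assumes that the same person records both times, which the fixed staffing makes likely.

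The size of any bias is unknown. The 14% to 41% with 86 per group, or 16% to 48% with 103, follows from an assumed shift and must not be read as an estimate of bias in this trial. Separately, and without any inference, the single-blind and double-blind descriptions contradict each other and need correcting.

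**What to change.** 1. Name who records FPS-R at T1 and T2. Place a screen or drape between that person and the ear from seed placement until the tapes are removed. A screen is preferable to a cap, which would obstruct continuous pressing.
2. Use the same recorder at T2, again without sight of the ear.
3. Leave observation of local skin reactions to the treating investigator, so that masking the recorder does not weaken safety monitoring.
4. Limit recorder training to outcome measurement and data entry. Leave out point locations, arm-specific procedure and randomisation.
5. Reconcile Study design with Randomization and blinding by stating which roles are blind and by what means.
6. For any patients assessed without masking, describe the recorder as potentially unblinded and do not call the trial double-blind. This may apply to many patients: recruitment was expected to end in December 2021 and the article appeared in May 2022.

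The cost is slight inconvenience at the bedside, a split training session and a short protocol paragraph. No extra visits are needed. A screen does not deal with patients mentioning what they feel, which belongs to the separate question of the patient's blind.
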